### Study design

The study comprises a randomised controlled trial (RCT) that is conducted in different (university) hospitals in the Netherlands. The study has two treatment arms in the first half year of the study: an arm in which participants will undergo an N=1-intervention and an arm in which they will receive usual care. The randomisation between these two arms is open-label and participants are randomised among those arms in a 2:1 ratio respectively. A 2:1 randomisation ratio ensures that the majority of participants receive the N=1 intervention, allowing for better-powered analyses for outcomes in which patients identified through the intervention as intolerant due to statin therapy or intolerant due to misattribution and/or nocebo effects are compared with each other. The randomisation will be stratified on study site and the use of ezetimibe at baseline and is performed in the data management system of the study. An overview of this study can be found in figure 1. Inclusions for this study began in April 2025, and we anticipate that the final participant will complete their last visit by December 2032.

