### Measurements and data collection

An overview of the study assessments at different moments during follow-up can be found in figure 1. During the study, participants will receive follow-up by means of clinic visits and by means of digital surveys. During study visits, HCPs will measure blood pressure, heart rate, weight, waist circumference and physical activity. They will also record lifestyle habits and record all medication dispensing data of the pharmacy and (changes in) medical history. HCPs will record their acceptability of the intervention using a questionnaire at 6, 12 and 24 months after randomisation.

During the 4 years of follow-up, participants will be asked to complete a survey on multiple timepoints of the study (figure 1). All items that these questionnaires consist of are:

demographics;self-reported medication use;barriers to medication adherence (open-ended question);reasons for stopping medication (open-ended question);changes in lifestyle (open-ended question);participant acceptability of N=1-intervention (self-made, non-validated questionnaire with statements about acceptability on a 5-point Likert-scale; disagree-agree);5-item Medication Adherence Reporting Scale (MARS-5);EuroQoL-5 Dimensions-5 Levels (EQ-5D-5L);Set of Brief Screening Questions (SBSQ);Beliefs about Medicines Questionnaire (BMQ);Patient Experiences and Satisfaction with Medication (PESaM);Decisional Conflict Scale (DCS);Wake Forest Physician Trust Scale (WFPTS);Psychological Inventory of Financial Scarcity on 4 items (PIFS-4);iMTA Medical Consumption Questionnaire (iMCQ);iMTA Productivity Costs Questionnaire (iPCQ).

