### Sample size calculation

A power analysis was performed to estimate the required number of participants for the study. This calculation assumed that 30% of patients will continue using statins after the N=1-intervention compared with 12% in the usual care group and included a drop-out margin of 25%. We have based the assumption that 30% of patients will continue statin therapy in the N=1-intervention arm of the study on four previous N=1-studies conducted in patients with statin intolerance that assessed the proportion of patients who restarted or were willing to restart statin therapy.^13 14 23 24^ Two of these studies reported the lowest lower bounds of the 95% Confidence Intervals (95% CIs) for this outcome of 29%.^23 24^ To ensure a conservative estimate for our power calculation, we therefore based our assumption on this lower bound. We have also assumed that 12% of patients in the usual care arm will continue statin therapy, which we consider a cautious estimate. However, we anticipate that some contamination bias may occur, as physicians may apply insights gained from the N=1-intervention arm in routine care, for example, through improved communication regarding statin intolerance and nocebo effects. This could lead to a higher proportion of patients in the usual care arm choosing to continue treatment.

Based on a two-sided alpha level of 0.05 and 80% power, our calculation showed that a total of 247 participants are needed for the study that has a 2:1 ratio of participants in the intervention and control arms respectively. Our trial has been funded for 249 participants, so we will include this amount of participants.

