### Data analysis plan

For our primary endpoint, the percentage of patients that continue their statin will be analysed by calculating an odds ratio that compares the participants randomised in the intervention and usual care arm and by calculating its associated 95% CI. Secondary endpoints will be analysed by applying the same strategy as for the primary endpoint with regard to categorical variables. For continuous variables, differences will be reported with a mean (SD) or median (IQR) depending on the distribution of the data and differences will be tested using a t-test or Mann-Whitney U test. For the cost-effectiveness analysis, an empirical cost-effectiveness analysis (CEA) and cost-utility analysis (CUA) will be conducted, which will employ seemingly unrelated regression equations (SURE), adjusted for baseline scores, baseline costs and quality of life.

In the case of missing baseline data, data will be imputed on the basis of other baseline characteristics like age, sex, Body Mass Index (BMI) and history of ASCVD. As convention, the outcome and follow-up values are not imputed. Spurious data will be cleaned from the dataset.

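### With no exception to the rule against imputing follow-up values, the cost-utility analysis and the cost side of the cost-effectiveness analysis become complete-case analyses

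*Protocol article*

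**What the plan says.** The Data analysis plan of the Protocol article names an empirical cost-effectiveness analysis (CEA) and a cost-utility analysis (CUA), "which will employ seemingly unrelated regression equations (SURE), adjusted for baseline scores, baseline costs and quality of life". Its next paragraph sets the missing-data rules. Missing baseline data are imputed from other baseline characteristics. For everything later, "As convention, the outcome and follow-up values are not imputed". No analysis is exempted.

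Measurements and data collection says that, over four years, "participants will be asked to complete a survey on multiple timepoints of the study". The instruments listed there include the iMCQ and iPCQ (care use and productivity costs) and the EQ-5D-5L (utilities). Planned outcomes makes cost-effectiveness a secondary outcome and indicates that the iMCQ and iPCQ are not its only sources. Pharmacy dispensing data are also recorded at study visits.

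The only attrition figure is in Sample size calculation, which "included a drop-out margin of 25" per cent.

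**The concern.** The primary endpoint is one yes/no answer at 12 months, so a survey missed at another time does it no harm. Economic totals are different. A cost or utility total over a period needs every wave in that period, and one gap leaves the total undefined unless the gap is filled. In its standard form, SURE also needs both the cost and the effect for each participant, so a missing total on either side removes the person from the model.

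Applied as written, the rule has two effects. It discards waves that were observed, including those completed before drop-out. It also makes the estimate depend on who completes everything. Allocation is open-label. During the N=1 periods one arm scores symptoms at least three times a week and gives blood in each period, while the other receives usual care, so completion may differ by arm. Symptoms and satisfaction with treatment could plausibly influence both survey completion and whether a patient stays on a statin or moves to a costlier drug. The model adjusts for baseline values only, while the observed follow-up waves carry the most information about a missing one.

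The Objectives section uses the cost-effectiveness analysis to judge feasibility and says positive results would guide adoption in routine care. The loss therefore matters even though the outcome is secondary.

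**Working it through.** **Step 1. Reproduce the plan's own figure.** The inputs from Sample size calculation are "Based on a two-sided alpha level of 0.05 and 80% power" and "30% of patients will continue using statins after the N=1-intervention compared with 12% in the usual care group". Allocation, from Study design, is 2:1.

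- Pooled proportion: (0.12 + 2 × 0.30)/3 = 0.24.
- Usual-care n = [1.960 × √(1.5 × 0.24 × 0.76) + 0.842 × √(0.12 × 0.88 + 0.30 × 0.70/2)]² / 0.18² = (1.025 + 0.386)² / 0.0324 ≈ 61.5, rounded up to 62.
- Total: 62 + 124 = 186. Inflated for drop-out: 186/0.75 = 248.

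The plan states "our calculation showed that a total of 247 participants are needed for the study". The difference of one is rounding: 3 × 61.5 ≈ 184.5, rounded up to 185, and 185/0.75 = 246.7, which rounds up to 247. So the 25% is applied as retention of 0.75, and the sample size itself is not in question.

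**Step 2. What the documented margin leaves.** Enrolment is 249, that is 166 and 83.

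- Total: 249 × 0.75 = 186.75, about 187.
- Intervention: 166 × 0.75 = 124.5, about 125.
- Usual care: 83 × 0.75 = 62.25, about 62.

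This is the complete-case economic sample if every retained participant completes every wave. Under the rule, the other 62 or so enrolled participants (249 − 187) contribute nothing to the totals, even for waves they completed.

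**Step 3. Illustration of missed waves.** The number of waves k, the per-wave completion r and the economic time horizon are not in the readable text (the schedule is in a figure that is not shown). The values of k and r below are therefore assumptions. With misses independent across waves and no separate drop-out, complete cases = 249 × r^k.

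| k | r = 0.95 | r = 0.90 | r = 0.85 | r = 0.80 |
|---|---|---|---|---|
| 3 | 213 | 182 | 153 | 127 |
| 4 | 203 | 163 | 130 | 102 |
| 6 | 183 | 132 | 94 | 65 |

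For k = 4: 249 × 0.95⁴ = 249 × 0.8145 = 203, and 249 × 0.90⁴ = 249 × 0.6561 = 163. Independence is pessimistic, because non-response usually clusters in the same people. The table shows how sensitive the sample is to k and r and is not a forecast.

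**Step 4. Which parts are affected.** The CUA needs utilities over time from the EQ-5D-5L, so it is affected directly. The CEA is affected through its cost total. Its effect measure is not stated and may be a single measurement. Dispensing data can supply some drug costs without a survey, but not utilities, productivity costs or wider care use.

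**The case against.** The case against has four parts.

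- **Condensed text.** The article gives the economic analysis one sentence, and its detail would normally sit in a full protocol or health-economic plan. The imputation sentence is a general convention that does not mention economic totals. This has some force, but the sentence is an affirmative rule on follow-up values with no exception, so the point does not rest on missing detail.
- **Size.** A reader might infer that the analysis will rest on a small remnant, perhaps half the participants. The documents do not support that. Applying four waves at 90–95% completion on top of the 25% margin gives 249 × 0.75 × 0.6561 ≈ 123 to 249 × 0.75 × 0.8145 ≈ 152. But the wave count and rates are assumed, and the stacking may double-count: self-reported medication use, which yields the primary outcome, is collected in the same surveys, so the margin may already cover some survey non-response.
- **Bias.** A reader might infer that complete-case SURE requires data missing completely at random, or that bias is certain. Neither follows. The regression is valid if completeness is unrelated to the outcomes given its covariates, and the plan adjusts for relevant baseline values. Dependence on follow-up experience beyond baseline is a plausible risk but is not shown.
- **Reliance on surveys.** Some cost inputs come from elsewhere, and the CEA effect may not be a sum over waves. This stands, and it limits the point to the CUA and the cost side of the CEA.

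**Conclusion.** The point holds as a defect in a stated rule. Followed literally, the Data analysis plan makes the CUA, and the cost side of the CEA, complete-case analyses wherever totals are accumulated over repeated surveys. Information from partly observed participants is lost, and validity depends on completeness being unrelated to costs and utilities given baseline covariates only.

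The documented size is a fall from 249 to about 187, with about 62 of 83 left in usual care. Any further reduction is conditional: 163–203 of 249 for four waves at 90–95% independent completion without separate drop-out. The sample may be materially reduced and selected, but the readable text does not establish that it will be. This is a secondary outcome, and the change is worth making because it is cheap and the result is meant to inform adoption.

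**What to change.** Amend the missing-data paragraph so that the no-imputation rule does not cover the economic analysis, and specify the following for it.

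1. Multiply impute missing wave-level costs and utilities separately by arm, using baseline values, observed waves, dispensing data and ezetimibe use.
2. Leave site out of the imputation model or collapse it. Study population gives at least 11 hospitals, so usual care has at most about 83/11 ≈ 7.5 patients per site on average.
3. Build the totals, run SURE in each imputed data set and pool with Rubin's rules. A likelihood-based longitudinal model for costs and utilities is an acceptable alternative.
4. Report the complete-case analysis as a sensitivity analysis and add a missing-not-at-random scenario.

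The cost is a change of wording and modest extra programming, with no new data. Inclusion began in April 2025 and the last visit is expected by December 2032, so there is time. The downside is that the main economic result would rest on a missing-at-random assumption, which the sensitivity analyses in item 4 are there to probe.

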### Planned outcomes

The primary outcome of the study is the incidence of self-reported statin use at 12 months after randomisation, which is a binary outcome measure (yes/no). We specifically chose this outcome as the primary endpoint because the main objective of the study is to determine whether N=1-interventions, compared with usual care, can increase statin use in patients in routine clinical practice. We considered the 12-month timepoint to be the most appropriate to evaluate this outcome, as we believe this timepoint, approximately 6 months after completion of the N=1-intervention, best reflects patients’ willingness to continue statin therapy in the longer term, beyond the immediate influence of the intervention. Secondary outcomes of this study are focused on use of cholesterol-lowering medication at different timepoints, cholesterol levels at different timepoints, cost-effectiveness, satisfaction with medication and multiple outcomes that assess the applicability of N=1-interventions in clinical care. All secondary outcomes that are studied are:

statin use;PCSK9i use;LDL-C levels;quality of life (EQ-5D-5L questionnaire);reported symptoms;cost-effectiveness (iMCQ and iPCQ questionnaire, among others);views on medication (BMQ questionnaire);satisfaction with statins (PESaM questionnaire);decisional conflict (DCS questionnaire);trust in the HCP (WFPTS questionnaire);HCP satisfaction with intervention (self-made, non-validated questionnaire with statements about acceptability on a 5-point Likert-scale; disagree-agree);treatment concordance during intervention;physical and mental complaints during intervention.

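### The primary odds ratio will use only participants with a 12-month self-report; loss related to statin use that differs by arm would bias it in either direction

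*Protocol article*

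**What the plan says.** Planned outcomes defines the primary outcome as "self-reported statin use at 12 months after randomisation, which is a binary outcome measure (yes/no"). The Data analysis plan analyses it by "calculating an odds ratio that compares the participants randomised in the intervention and usual care arm", with a 95% confidence interval. The same section imputes missing baseline data and then states: "As convention, the outcome and follow-up values are not imputed". The article gives no rule for classifying a participant whose 12-month answer is missing.

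The Sample size calculation works from these rates: "30% of patients will continue using statins after the N=1-intervention compared with 12% in the usual care group". For loss to follow-up, that section says that it "included a drop-out margin of 25" per cent. Study design makes allocation between the arms open-label at 2:1. Under Measurements and data collection, healthcare professionals at study visits "record all medication dispensing data of the pharmacy and (changes in) medical history", but nothing links the dispensing data to the primary outcome.

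**The concern.** With no imputation and no default classification, a participant without a 12-month answer cannot enter the odds ratio. The article does not use the words complete-case analysis, but that is what the rule amounts to. The analysis is described as comparing the randomised arms, yet the rule cannot deliver this for everyone randomised once answers are missing.

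Loss could plausibly differ between the arms. N=1 participants go through four blinded 6-week periods with symptom scores at least three times a week and a blood draw in each period; usual care has none of this. Everyone enrolled has already reported side effects on at least two statins, so someone who stops again may also stop answering. At stake is whether the primary result reflects the intervention or who stayed to report. Calling the rule a convention does not make it neutral.

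**Working it through.** **1. The plan's own figure.** Inputs from the Sample size calculation: 30% versus 12%, 2:1, two-sided alpha 0.05, 80% power, 25% drop-out. The pooled-variance formula for two proportions gives 61.5 usual-care and 123.0 N=1 participants. Rounded up, 62 + 123 = 185, and 185/0.75 = 246.7, which rounds to the stated 247. (Fixing 62 and doubling it gives 186/0.75 = 248.) The margin is thus applied as N/(1 − d). With 249 randomised (166 and 83), the design allows for 249 × 0.25 ≈ 62 participants without a primary outcome; power among the remaining 187 or so is about 80%.

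**2. When the odds ratio is biased.** Let r be the probability of having a 12-month answer, for users (u) and non-users (n) in each arm. Among those who answer,

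observed OR = true OR × B, where B = (r_u/r_n in N=1) ÷ (r_u/r_n in usual care).

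If loss is unrelated to statin use, r_u = r_n in each arm and B = 1, however unequal the drop-out. For example, random loss of 25% versus 10% leaves a null odds ratio at 1.00. If only non-users are lost, at equal rates, and true use is equal in both arms, B is again 1. Bias needs the relation between loss and use to differ by arm.

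**3. Size.** All losses by arm, and their relation to statin use, are assumptions. A split of 30% (N=1) and 15% (usual care) averages (166 × 0.30 + 83 × 0.15)/249 = 25%.

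- *No true effect, use 15% in both arms, only non-users lost, 30% versus 15%.* Observed use is 0.15/0.70 = 21.4% versus 0.15/0.85 = 17.6%. OR = (0.214/0.786)/(0.176/0.824) = 1.27. With about 116 versus 71 answering, a pooled z-test rejects about 9% of the time, against a nominal 5%.
- *Design rates among those who answer, same losses.* 0.30 × 0.70 = 21.0% and 0.12 × 0.85 = 10.2% of those randomised. The difference falls from 18 to 10.8 points and the OR from 3.14 to 2.34.
- *Losses reversed, 15% versus 30% (20% overall), only non-users lost, no true effect.* OR = 0.79, 0.77 and 0.73 at true use of 12%, 20% and 30%. This pattern would hide a benefit.
- *Equal 25% loss, different reasons: only non-users lost in N=1, random loss in usual care, no true effect.* OR = 1.40, 1.45 and 1.56 at true use of 12%, 20% and 30%; a Wald test on the log odds ratio rejects 11%, 17% and 27% of the time.

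**4. How easily the conclusion could turn.** At the design rates with 25% lost per arm, about 37/124 versus 7/62 are users: OR 3.34 (95% CI 1.39 to 8.02). Counting all missing participants as non-users gives 37/166 versus 7/83: OR 3.11 (1.32 to 7.33). If just 3 of the 21 missing usual-care participants are users while all missing N=1 participants are not, the table is 37/166 versus 10/83: OR = (37 × 73)/(129 × 10) = 2.09 (0.98 to 4.46), no longer significant.

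**The case against.** The article is condensed, and sensitivity analyses and analysis sets are commonly left to a statistical analysis plan. That stands: their absence is not the finding. The finding is the rule that the article does state, which an analysis plan imputing the primary outcome would contradict.

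The mechanism is assumed. This also stands: the 25% is a planning margin, not a forecast by arm or by statin use; losing only non-users is the extreme case; and the 9% rejection rate in the first null scenario is a modest excess.

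Four stronger readings are tempting and are not supported.

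- A reader might infer that the result favours the intervention whenever N=1 drop-out is the higher. It does not if loss is unrelated to statin use, and the bias can run the other way.
- A reader might infer that dispensing data would settle most missing answers. They are recorded at study visits, so those who stop attending may lack both sources.
- A reader might infer that missing participants should simply count as non-users in the primary analysis. With true use of 15% in both arms and random loss of 30% versus 15%, that rule gives 0.15 × 0.70 = 10.5% versus 0.15 × 0.85 = 12.75%, OR 0.80. With the losses reversed it gives 1.25. Complete cases give 1.00 in both.
- A reader might take the power of about 77% under that rule as the worst case. It holds only for equal 25% loss (see the fix).

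**Conclusion.** The concern holds in a limited form and should be fixed. The stated rule confines the primary odds ratio to participants with a 12-month self-report, in an open-label trial sized for the loss of a quarter of its participants. It is safe only if loss is unrelated to statin use, or related to it in the same way in both arms; the rule itself offers no check on either condition.

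Under the assumed losses, a null effect appears as an odds ratio between about 0.73 and 1.56, depending on direction and mechanism, and an apparent 3.14 may be 2.34 among all randomised. These figures show what could happen. The documents do not establish that loss will be differential or which arm it would favour.

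**What to change.** Replace the no-imputation sentence as it applies to the primary outcome:

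1. Analyse all randomised participants in their allocated arm.
2. Where the 12-month self-report is missing, use the pharmacy dispensing record where one is available.
3. Handle the rest by multiple imputation within arm, using baseline and follow-up data including dispensing.
4. Add sensitivity analyses: complete cases; missing counted as non-user; and a tipping-point analysis that varies the missing outcomes separately by arm.
5. Report missingness by arm.

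The cost is some extra analysis work and no additional participants. Dispensing is a slightly different measure from self-report and may itself be missing for those who stop attending. The missing-as-non-user analysis has less power than the plan's 80%. By a pooled z-test with 166 versus 83, power is about 77% with equal 25% loss at the design rates (0.30 × 0.75 = 22.5% versus 0.12 × 0.75 = 9%), and about 57% if use is 21.0% versus 10.2% of those randomised. This is one reason to keep it as a sensitivity analysis.
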